#### Older community members: comparator

3.5.2

Given the proposed whole of community impact of *Connect Local* program, the inclusion criteria for the comparator group are the same as for the intervention group, except that they do not live in the target LGA. These participants will be recruited from the local tertiary hospital and aged and community care provider. All eligible individuals will be made aware of the program through their care provider and will be asked if their details can be shared with the researchers to contact them about the study. The researchers will contact the individuals to obtain consent. Recruitment will be monitored in blocks of five to match comparator participants by age and gender to the intervention participant group.

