### Program effectiveness

3.1

Compared to the comparator group, older people receiving the intervention will, when compared to baseline, report at 3-, 6- and 12-months follow-up:

(i) a reduction in loneliness, social isolation and/or depressive symptoms;(ii) improvement in wellbeing and quality of life;(iii) increased access to activities/services in the community.

Three months after participation in the program, community volunteer participants will have improved wellbeing and quality of life when compared to baseline.

It is hypothesised that all stakeholders: intervention, volunteer and service provider participants will also have a positive perception of and experience with the program.

*Research question for older participant cohort using PICO:*

Does participation in the *Connect Local* social connection program reduce loneliness, social isolation and/or depressive symptoms, improve wellbeing and quality of life and increase access to activities/services in community of older Australians when compared to a similar group who do not have access to a similar program?

*Research question components for stakeholders using SPIDER:*

Sample: volunteers and service provider participants;

Phenomenon of interest: perception and experience of program;

Design: prospective surveys and semi-structured interviews;

Evaluation: impact on community and health services, and perceptions of the program;

Research type: mixed methods.

Question: What are the perceptions and experiences of volunteers/service provider participants after being a part of the *Connect Local* program?

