### Implementation: *Connect local* will be implemented as planned

3.3

The program effectiveness and cost-effectiveness components will be evaluated in a prospective, cohort quasi-experimental (non-randomised), pragmatic trial, using a convenience sample of participants, with the intervention group drawn from those living in the target LGA who access the community connector.

*Research question components using SPIDER:*

Sample: older community members, volunteers and service provider participants;

Phenomena of interest: reach, adoption, feasibility, appropriateness, fidelity, sustainability.

Design: prospective surveys, semi-structured interviews, administrative data;

Evaluation: implementation of program as planned;

Research type: mixed methods.

Question: What are the perceptions and experiences of [participants] about the *Connect Local* program and it being implemented as planned?

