### The intervention: *Connect Local*

3.4

The *Connect Local* program will involve eligible individuals to access a trained and paid Community Connecter professional. Community Connectors are individuals with a counselling, community development, health/allied health professional and/or life coaching background, who receive training in social prescribing (55), wellness and reablement and positive ageing, diversity in ageing, mental health first aid and trauma informed care.

Once a referral/contact is received, the *Connect Local* program manager contacts the community member and first discusses the program, to ascertain that it is what they are seeking. If so, the community member is screened for eligibility, namely, they live in target geographic location, are aged 65 or older, have a chronic health condition, and are in need of social connection. If appropriate, the program manager organises the Community Connector to contact the individual to organise a time to meet face to face and commence the program. As shown in Figure 3, the Community Connector will work with eligible community members to:

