#### Comparator group (usual care)

3.4.1

These individuals will receive usual care (regular access to activities in their LGA), and will not be engaged in the *Connect Local* program.

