Health system level *Impacting at the health service level, including hospitalisations, GP visits and other health service visits.*	*Older person participants:*	
	ED presentations; Hospitalisations; Hospital length of stay Number of GP consultations Number of GP care plan reviews	Resource use questionnaire [adapted from Fletcher et al. (65)]
	*Health Service providers:*	
	Perspectives of staff in general practice and other referral agencies Health provider satisfaction	Interviews/focus groups

^+^Data not being collected from community members in comparator group.

The exclusion criteria include living in residential aged care; individuals who do not speak English sufficiently to understand the program; and individuals who do not have the cognitive capacity to consent [assessed using a Cognitive Capacity to Consent Checklist (67)].

All eligible individuals will be made aware of the evaluation by the Community Connector and asked if their details can be shared with the researchers to contact them about the study. The researchers will contact the individuals to obtain consent. If consent is obtained, individuals will be asked if they would like to be informed of trial results.

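### Only the intervention group is selected on seeking the program; comparators are not asked whether they would want such help, and the criteria do not ensure they lack a similar program

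*Protocol article*

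**What the plan says.** **Intervention entry.** Section 3.3 describes a non-randomised convenience sample, "with the intervention group drawn from those living in the target LGA who access the community connector". Section 3.4 gives the order of steps. After a referral or contact, the program manager "first discusses the program, to ascertain that it is what they are seeking". Only if so is the person screened for residence, age and the remaining conditions, which are that they "have a chronic health condition, and are in need of social connection".

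**Comparator entry.** Section 3.5.2 says the inclusion criteria for "the comparator group are the same as for the intervention group, except that they do not live in the target LGA". On the source it says: "These participants will be recruited from the local tertiary hospital and aged and community care provider". Care providers tell eligible people about the program and ask whether their details may be passed to the researchers, who then seek consent. Matching is by age and gender, monitored in blocks of five.

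**Comparison intended.** The research question in 3.1 asks about effects "when compared to a similar group who do not have access to a similar program". Section 3.2 puts the economic question as a comparison with no Connect Local. Section 3.4.1 says of comparators: "These individuals will receive usual care (regular access to activities in their LGA"), and adds only that they will not be engaged in Connect Local. The exclusions under 3.5.1 cover residential aged care, insufficient English and lack of capacity to consent.

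**Analysis.** Section 3.7.1.1 specifies mixed models with group, time and group-by-time terms. Community-level and system-level variables are analysed descriptively.

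**The concern.** In a non-randomised comparison, the comparator shows what the intervention group would have done without the program only if the two groups are alike in whatever drives change in the outcome. Wanting to become more connected is a plausible driver of change in loneliness. The intervention group is selected on it and the comparator group is not. If people who want connection tend to change differently on UCLA-3 without any program, that difference enters the primary contrast and is credited to Connect Local.

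The second issue concerns the definition of the comparator. The research question promises people without access to a similar program, but no listed criterion secures this. If some comparators use a link-worker, visiting or peer-support scheme, the estimate no longer answers the question as 3.1 words it. The same group supplies the deadweight percentage in Box 1, so the social return calculation depends on which comparison is meant.

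**Working it through.** The plan gives no figure on this point to reproduce, so the check sets the sections side by side and uses simple algebra.

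**1. Is the entry step one-sided?**
- Intervention: refers or is referred, confirms that the program is what they seek (3.4), is screened (3.4, 3.5.1), accesses the connector (3.3), consents.
- Comparator: is identified by a care provider, agrees to contact about a study, consents (3.5.2). There is no question about wanting help.

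The list in 3.5.1 does not contain the seeking step, so the sentence in 3.5.2 is literally correct. The mismatch is between 3.3/3.4 and 3.5.2.

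**2. Do matching or the model remove it?** Write *e* for the program effect, and *s_I* and *s_C* for the mean changes in UCLA-3 that would occur without any program in the intervention and comparator groups.
- Expected contrast in change = (*e* + *s_I*) − *s_C* = *e* + (*s_I* − *s_C*).
- The group term absorbs a difference in baseline level. The group-by-time term carries *s_I* − *s_C* together with *e*.
- Matching on age and gender removes only what those two variables explain.
- Table 3 lists no measure of wanting help, so it cannot be adjusted for afterwards unless it is recorded at entry.

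**3. Do the criteria deliver the comparator in 3.1?** Section 3.1 requires no access to a similar program. Section 3.4.1 bars only Connect Local, and the listed exclusions do not mention similar programs. The criteria therefore do not ensure that comparator.

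**4. What would similar-program use do?** Suppose, with additive effects, that a share *p* of comparators and a share *q* of intervention participants use such a program with benefit *b*.
- Contrast = *e* + (*s_I* − *s_C*) − (*p* − *q*)·*b*.
- Excluding users from the comparator only sets *p* = 0 and leaves + *q*·*b*, which is a new one-sided difference.
- Omitting users from both groups sets *p* = *q* = 0.

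**5. Is similar-program use recorded?** Table 3 schedules the Resource use questionnaire at baseline, 3, 6 and 12 months. Section 3.6.2.2 says it captures the number and types of services offered and used in both groups. Its items are not shown. It is not an eligibility check, and the planned analysis of it is descriptive.

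**6. Size.** The document gives no value for *s_I* − *s_C*, *p*, *q* or *b*. As an assumption only: if *b* = *e*, *q* = 0, *s_I* = *s_C* and *p* is 10% to 20%, the contrast is *e*(1 − *p*), that is 90% to 80% of *e*.

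**The case against.** Several objections stand, and they limit the point.

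- **Need for social connection is not an extra criterion.** It is a short form of the 3.5.1 criterion on risk or presence of loneliness, isolation or depressive symptoms, which comparators must also meet. The asymmetry rests on seeking alone.
- **Symptom thresholds are shared.** Regression to the mean caused by those thresholds applies to both groups. Section 3.4 also lists hospital, aged care, general practice and allied health among the sources of intervention participants, so not all of them come forward unprompted. They still pass the seeking step.
- **Services used are already planned data in both groups.** It would be wrong to say that similar-program use cannot be examined.
- **Under the comparison in 3.2, other services belong to the counterfactual.** Deadweight in Box 1 is what would be attained without the activity, so such use does not inflate it on that reading. The problem is that 3.1 and 3.2 imply different comparators.
- **The article condenses a fuller protocol**, and both lists of criteria are introduced as inclusive. Further screening items may exist. What is shown nevertheless describes the two routes of entry in enough detail to see that they differ.

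A reader might infer that the comparator is definitely not the group in the research question. The document does not support that, because it does not say whether similar programs operate outside the target LGA. A reader might also set a guessed help-seeking effect against the 0.85-point UCLA-3 reduction in 3.6.2.3.1. That figure is a mean reduction reported by another program and is not stated to be this trial's between-group contrast, so such a percentage would mean little.

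**Conclusion.** The point holds in two parts. First, selection on seeking the program applies to the intervention group only, and neither the matching nor the stated model deals with it. Part of any difference in UCLA-3 change may therefore be due to help-seeking. Second, the criteria do not ensure the comparator named in 3.1, and 3.1, 3.2 and 3.4.1 do not agree on which comparison is meant.

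The size is unknown. If help-seekers improve more without a program, the first bias favours Connect Local. Similar-program use among comparators would work against it. The two need not cancel, and the net direction cannot be stated. The conclusion assumes that wanting help is related to change in loneliness, which is plausible but not shown in the document. The change is worth making because motivation at entry cannot be recovered reliably later and costs little to record.

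**What to change.** 1. **Section 3.5.2:** add a yes/no screening question asking comparators whether they would want help to find and join local activities or services if it were offered, and enrol those who answer yes. At minimum, record the answer at baseline and restrict comparators to those answering yes in a sensitivity analysis. A hypothetical question is an imperfect stand-in for actual seeking, so it reduces the difference without removing it.
2. **Resource use questionnaire:** record current use of link-worker, social prescribing, visiting or peer-support programs other than Connect Local, in both groups, at baseline, 3, 6 and 12 months. Add a sensitivity analysis of the primary outcome that omits users in both groups. Do not exclude them from the comparator alone. Uptake after baseline may itself result from Connect Local, so this analysis is supportive only.
3. **Sections 3.1, 3.2 and 3.4.1:** state one comparison, either no similar program or no Connect Local, and apply it also to deadweight in Box 1.
4. **Wording of 3.5.2:** keep the statement that the criteria listed in 3.5.1 differ only by residence, and add that the intervention group also passes the program-entry step in 3.4.

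The cost is a protocol amendment, one screening question, a short addition to a questionnaire already scheduled, and somewhat more comparator screening to fill each block of five.

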**Figure 3 fig3:**
[figure not shown]
Service flow of *Connect Local*. Adapted from Mann et al. (20).

Individuals who participate in all four elements will be considered to have completed the full program. Meetings between the Community Connector and the participant will be undertaken in a mutually agreed upon location, including local community houses, local spaces such as libraries, local cafés, or in the participant’s home.

People will be engaged in the program through multiple sources: the local tertiary hospital, aged care provider, general practices, allied health providers, community health providers, through the program website, and general community access.

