##### System level

3.6.2.3

To evaluate impact of *Connect Local* on health services use such as hospitalisations, General Practitioner (GP) visits and other health service visits, several health service-related indicators will be collected from participants in both the intervention and comparator groups at baseline, 3, 6 and 12 months using the Resource Use Questionnaire [adapted from Fletcher (65)], as per Tables 2, 3. Using interviews, the service provider morale in general practice and other referral agencies and healthcare provider satisfaction will also be gathered at three months from when their patients engaged in the *Connect Local* program.

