For quantitative, binary or dichotomous individual level outcomes (scales that have cut-off scores: loneliness (UCLA-3), social anxiety, depressive symptoms) additional analysis will be undertaken addressing the research question: do the interventions differ in their effectiveness, such that individuals in the intervention group experience a greater improvement in their probability of achieving the desired outcome compared to those receiving usual care. Generalised linear mixed models (GLMMs) for dichotomous outcomes will be used as well as GEE. The typology of missing data will be investigated to make sure that the assumptions of the adopted statistical technique are not violated. Our choice of GLMMs is based on the specific characteristics of the data, as well as the advantages provided by GLMMs in handling dependent responses in longitudinal or repeated measures studies. As highlighted in Breslow and Clayton (75), GLMMs incorporate random effects into the linear predictors and are particularly well-suited for modelling the dependence among response variables in such study designs.

Selection of the model that best fits the data will be based on the low goodness-of-fit measures such as the Akaike information criterion (AIC) and Bayesian information criterion (BIC). Additionally, the log-likelihood ratio test will be employed as another method for evaluating model fit.

All quantitative community and system level variables, as well as the goal attainment will be analysed descriptively. Descriptive statistics will be presented as proportions, means (standard deviations) or, for variables that did not conform to a normal or log-normal distribution, medians (interquartile range).

Statistical analysis will be performed using STATA V.15.0 (STATA Corp LP., College Station, Texas, United States). We will use a Type I error rate of 5% to indicate statistical significance, with 95% confidence intervals (CI).

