**BOX 1 Tools used to calculate Social Return on Investment (SROI)**

**Tools of SROI**
Establishing impact (attribution, deadweight, displacement, drop-off):To minimise the risk of overclaiming the benefits it was necessary to account for deadweight, displacement, attribution, and attrition.*Deadweight:* responds to the question: ‘How much of the outcome would still be attained without the activity delivered?’We will use the quantitative data captured in the comparator group to ascertain this information, measured as a percentage, and then that percentage of the outcome will be deducted from the total quantity of the outcome.*Displacement* responds to the question: ‘Were there any activities with the same outcome displaced by the intervention being evaluated?’We will capture this information when collecting service information from participants involved in the program and comparing them to what was captured in the comparator group – using a percentage and deducted from the total outcomes.*Attribution* responds to the question; ‘Who else contributed to the attainment of the outcome?The research team will identify all relevant stakeholders and to assess how much of each outcome could be attributed to the delivery of Connecting Communities to Care with due circumspection. This will be calculated as a percentage.*Drop-off* responds to the question: ‘How much of the outcome is lost in the years post intervention?’To calculate the percentage of the outcome lost in the years after delivery of the intervention. It is calculated by deducting a fixed percentage from the remaining level of outcome at the end of each year. This will be calculated as a percentage.

*Calculating the SROI:*

The calculation of the SROI will consider the total value of the inputs in the program. The discounted, monetised value of benefits and outcomes will be divided by total investment (inputs) to estimate the SROI ratio.

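### Comparators come only through a hospital and an aged care provider, so an unequal hospital-recruited share could bias the hospital-use contrast and the service-use part of the SROI deadweight

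*Protocol article*

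**What the plan says.** The design is a "cohort quasi-experimental (non-randomised), pragmatic trial, using a convenience sample of participants" (section 3.3). On the comparator, section 3.5.2 states: "These participants will be recruited from the local tertiary hospital and aged and community care provider". Recruitment is monitored in blocks of five to "match comparator participants by age and gender to the intervention participant group"; no other matching factor is named.

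The intervention group is drawn from more places. Section 3.4, after Figure 3, lists "the local tertiary hospital, aged care provider, general practices, allied health providers, community health providers, through the program website, and general community access".

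Hospital use is an outcome in both groups. Table 2 names ED presentations, hospitalisations and length of stay, and section 3.6.2.3 says "several health service-related indicators will be collected from participants in both the intervention and comparator groups at baseline, 3, 6 and 12 months". On analysis, section 3.7.1.1 states: "All quantitative community and system level variables, as well as the goal attainment will be analysed descriptively".

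The same data feed the economic evaluation. Section 3.6.3.1 includes health service use among the outcomes compared between groups and then monetised. For deadweight, Box 1 says "We will use the quantitative data captured in the comparator group to ascertain this information, measured as a percentage", and that percentage is then deducted from the program's outcome.

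**The concern.** Contact with a hospital is one of only two ways into the comparator group, and contact with a hospital is also something the evaluation counts. If a person is recruited around an admission or ED visit, and that episode sits in the baseline count, the count will tend to be lower at the next assessment whatever happens in between. This is regression to the mean produced by sampling.

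The intervention group is exposed to the same effect, but only for the part of it that comes through the hospital. With five further routes into the program, that part may well be smaller. Age and gender matching does not balance it. The mixed models in section 3.7.1.1 cover individual-level scales, so they do not reach service use either.

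At stake are the between-group contrast in hospital use and the service-use part of the deadweight. There, a fall in the comparator is treated as change that would have happened without the program.

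**Working it through.** The plan gives no figure to reproduce on this point, so the check is of mechanism and plausible size.

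**Inputs from the article.** Two comparator routes (3.5.2); seven intervention routes, including the same two (3.4); matching on age and gender (3.5.2); 88 people per group (3.6.2.3.1); deadweight from comparator data as a percentage (Box 1).

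**Inputs not in the article, assumed here.** The hospital-recruited share in the comparator (p_c) and intervention group (p_i), the admission rate, and that each hospital recruit has a recruiting episode inside the baseline window.

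**Step 1: simple version.** Each hospital recruit carries one extra episode at baseline and none afterwards, and the program has no effect. The spurious difference in change per person is p_c − p_i.

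| p_c | p_i | Difference per person | Across 88 people |
|---|---|---|---|
| 50% | 50% | 0 | 0 |
| 50% | 30% | 0.20 | 0.20 × 88 ≈ 18 |
| 50% | 20% | 0.30 | 0.30 × 88 ≈ 26 |

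**Step 2: allowing for readmission.** Let each person's 3-month count be Poisson, with a personal rate that is gamma distributed with mean m and shape k. Hospital recruits are those with at least one episode at baseline; everyone else is unselected and has no expected change. With P0 = (k/(k+m))^k:

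- baseline mean in hospital recruits = m/(1 − P0)
- follow-up mean = (m − P0·km/(k+m))/(1 − P0)

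For m = 0.2 and k = 0.5, P0 = 0.845. The baseline mean is 0.2/0.155 = 1.29, the follow-up mean is (0.2 − 0.845 × 0.143)/0.155 = 0.51, and the fall is 0.78. Over m = 0.1–0.2 and k = 0.5–1.0 the fall is 0.78–0.91 per hospital recruit. The difference in change is (p_c − p_i) times this:

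- 50% v 30%: 0.20 × 0.78 = 0.16 to 0.20 × 0.91 = 0.18
- 50% v 20%: 0.30 × 0.78 = 0.23 to 0.30 × 0.91 = 0.27
- equal shares: 0

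A simulation of the same model gave 0.23–0.27 for 50% v 20% and 0 at equal shares.

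**Step 3: what reaches the deadweight.** Take 50% v 20%, a background of 0.15 episodes per period and a true 20% reduction (0.03), using the simple version. The comparator goes from 0.15 + 0.50 = 0.65 to 0.15, a fall of 0.50. The intervention group goes from 0.15 + 0.20 = 0.35 to 0.12, a fall of 0.23. Box 1 can be read in two ways.

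- Comparator fall relative to intervention fall: 0.50 exceeds 0.23, so deadweight passes 100%.
- Comparator's own percentage change: 0.50/0.65 = 77%. Deducting it leaves 0.23 × (0.15/0.65) = 0.053, more than the true 0.03.

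The two readings err in opposite directions.

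**Step 4: recruiting episode excluded.** The comparator goes from 0.15 to 0.15 and the intervention group from 0.15 to 0.12. Deadweight is 0 on either reading, and 0.03 is recovered.

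**The case against.** The case on the other side has several sound parts.

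- The article does not say that hospital recruitment means a recent admission or ED visit. People approached through outpatient or community clinics would bring no such episode. The questionnaire's look-back window is not given, and in a condensed article both details may sit in the full protocol. This stands, and it makes the concern conditional.
- The hospital and the aged care provider also feed the intervention group, and eligibility is the same apart from area of residence. This stands too: the bias in the contrast depends on a difference in shares. But no stated step keeps the shares alike.
- Service use is not the primary outcome and is only described, so no significance test is distorted. This stands and limits the importance of the point.

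A reader might infer that the artefact would wipe out the program's benefit, or settle the SROI hypothesis in section 3.2(ii). The documents support neither. Box 1 does not define the deadweight percentage, and on one natural reading the benefit is overstated (step 3). The SROI also adds up loneliness, social connection, depressive symptoms, wellbeing and quality of life, with no weights given, so hospital use is one part of one component.

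A reader might also want deadweight based only on source-stratified results. The strata would be too small: at a 20% share, about 18 of 88 intervention participants, with 18 × 0.15 ≈ 2.7 expected episodes per period. Participants from the other five routes would have no comparator.

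**Conclusion.** The concern holds as a conditional risk. The recruitment frame, the matching factors, the descriptive analysis and the source of deadweight are all stated, and nothing stated prevents unequal hospital shares from biasing the service-use contrast and its deadweight. The actual size cannot be computed, because the article gives no source shares, look-back window or deadweight formula. With assumed shares of 50% v 20–30% and one recruiting episode per hospital recruit, the spurious difference in change is about 0.2–0.3 episodes per person (0.16–0.18 for 50% v 30% when readmission is allowed for). It is zero at equal shares.

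The direction is not fixed either. A larger hospital share in the comparator makes its fall too large and works against the program when changes are compared. A larger share in the intervention group does the reverse. If follow-up levels were compared instead, a comparator with more hospital recruits would tend to favour the program.

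The loneliness outcome is outside this point. The change is worth making as a cheap improvement.

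**What to change.** 1. For every participant, record the recruitment source and whether a hospital episode led to recruitment.
2. In section 3.5.2, add hospital versus non-hospital source to the block-of-five monitoring as a balancing target where feasible.
3. In section 3.6.2.3, exclude the recruiting episode from the baseline counts of ED presentations, hospitalisations and length of stay, in both groups.
4. In Box 1, compute the service-use contrast and its deadweight on these counts, and state the deadweight formula. Give a source-stratified or source-adjusted version as a sensitivity analysis.
5. State that intervention participants from the other routes have no source-matched comparator for these outcomes.

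The cost is slightly more data collection, slower comparator recruitment if the balancing target binds, and stratified estimates that will be imprecise. Source has to be recorded at enrolment, since it may not be recoverable later.
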